##### Day 90 data collection

The day 90 data are collected from routine medical records. The information being obtained is summarised in table 2.

**Table 2 T2:** Data collected at day 90

General follow-up from baseline	Results from investigations requested at the study entry TIA clinical review Any diagnosis change between TIA clinical review and day 90 assessment Vital status at day 90 (alive/deceased)
Stroke occurrence	If a stroke(s) has occurred, the following are obtained: Date/time of stroke Stroke symptoms (National Institute of Health Stroke Score) Stroke location (Oxford Community Stroke Project classification) Stroke type (infarction/haemorrhage) Investigations performed with reports (CT/CTA/MRI/MRA/other brain imaging) Treatments received (thrombolysis/thrombectomy/aspirin/clopidogrel/dipyridamole/ticagrelor/warfarin/dabigatran/rivaroxaban/apixaban/edoxaban/other anticoagulant/statin/other cholesterol treatment/blood pressure medication/carotid endarterectomy)
Further TIA and/or migraine symptoms occurrence	If further TIA and/or migraine symptoms have occurred, the following are obtained: Date and time of episode Review by TIA team Review by other service Diagnosis given (TIA/migraine/other) Investigations performed reports (CT/CTA/MRI/MRA/other brain imaging) Treatments received (aspirin/clopidogrel/dipyridamole/ticagrelor/warfarin/dabigatran/rivaroxaban/apixaban/edoxaban/other anticoagulant/statin/other cholesterol treatment/blood pressure medication/treatment for migraine or headaches/carotid endarterectomy) Other neurological events leading to hospital attendance or admission which occurred within the last 90 days
Medication side effects	If new medications were commenced at the study entry TIA clinical review: Free text description of any side effects Medication discontinued

TIA, Transient ischaemic attack.

### Adjudication of stroke diagnosis

In order to ensure that there is confidence in all episodes of stroke, TIA or migraine recorded by participating hospital sites between study entry and day 90, every event will be independently adjudicated by a study panel comprising five stroke or neurology specialists, organised and managed by the study co-ordinating centre team at Newcastle University. The panel will be provided with the clinical features including acute symptoms, clinical radiological reports and treatments received and asked to assign a diagnosis of stroke, TIA or migraine. The panel will not be provided with the diagnosis assigned by NHS site nor the original specialist more likely diagnosis (migraine or TIA with migrainous symptoms) at study entry.

If there is disagreement between the panel and the participating hospital diagnosis, the relevant hospital will be contacted to obtain any additional clinical information, which will subsequently be presented back to the panel. If the disagreement cannot be resolved despite additional information, these cases will be labelled as ‘unclear’ and will not be included in development of the risk assessment.

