### Sample size

The sample size calculation is based on the premise that clinician-assigned more likely diagnosis currently does not separate the study population into groups with significantly different risks of stroke. As it is currently unknown whether the 90 day risk of stroke following a likely diagnosis of TIA with migrainous symptoms is the same as typical TIA (ie, 10%) and how this might be affected by prevention treatments, to power this study the TIA with migrainous symptoms event rate has been conservatively set much lower at 1%. The day 90 risk of stroke in the migraine group has been set at 0.015% based upon the previously reported average incidence of stroke in true migraine sufferers 58/100 000 patients/year.^22^,^24^ At 90% power and a two-sided significance level of p=0.05, a total of 2574 participants (1287 per group) are required to detect this difference (or a greater difference) in stroke rate between specialist assigned more likely diagnosis of migraine and TIA with migrainous symptoms groups. Inflating for a 5% loss in case of routine data access difficulties or allocation of an ‘unclear’ independent adjudication label for any observed outcome events results in an overall target of 2709 participants.

A cohort of this size is also sufficient to examine whether stroke can be predicted by multiple explanatory variables. If the stroke rate in the TIA with migrainous symptoms group is the same as previous TIA cohorts (10%), then at least 128 outcome events are expected.

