#### Prognostic model and risk assessment tool development

Development of the risk assessment tool will combine information from both Study A and Study B. Using the stages described by Moons *et al*^25 26^ and applying Transparent Reporting of a Multivariable Prediction Model for Individual Prognosis or Diagnosis (TRIPOD) Statement principles,^27^ a prognostic model will be developed through multiple regression to examine the association between clinical characteristics recorded during initial specialist TIA review (including demographics, symptoms and previous medical history) and the 90 day occurrence of any stroke. The initial model will contain all baseline factors independently associated with day 90 stroke and those nominated as plausible by clinicians during Study B initial co-design rounds. Backward stepwise regression will retain variables for the final prognostic model. The performance of the model will be summarised using calibration and discrimination measures. To correct for overfitting and optimism in model performance, an internal validation using bootstrap samples will be performed which splits the data into training and test samples multiple times.

Approaches to visually represent the prognostic model (eg, nomogram)^28^ will be prepared and shared with clinicians during the final round of the study B co-design process to confirm clinical sense and meaning. These will include simple and more complex risk tool options and their matching predictive performance statistics. Options will include clinician preferences about risk assessment tool format identified during the earlier co-design rounds. The final tool preferred by clinicians is expected to reflect a balance between predictive performance and a format/content which is suitable for real world clinical use^29^ e.g. it can be completed within the time restrictions of clinical care with information that is often available, while retaining acceptable utility.

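### Participants whose follow-up event stays in dispute between panel and hospital are dropped from the prediction model: a selection on outcome information that, as worded, also covers TIA-versus-migraine disputes in which neither label is a stroke

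*Protocol article*

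**What the plan says.** All from the protocol article.

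- **Adjudication of stroke diagnosis, scope and labels.** The scope is "all episodes of stroke, TIA or migraine recorded by participating hospital sites between study entry and day 90, every event will be independently adjudicated". The panel is "asked to assign a diagnosis of stroke, TIA or migraine", so there are three labels.
- **Same section, masking.** "The panel will not be provided with the diagnosis assigned by NHS site nor the original specialist more likely diagnosis". No masking is described for the hospital.
- **Same section, disagreement.** "If there is disagreement between the panel and the participating hospital diagnosis, the relevant hospital will be contacted to obtain any additional clinical information". The new information goes back to the panel. If the two still differ, the case is labelled 'unclear', and such cases "will not be included in development of the risk assessment". Nothing limits this to disputes about whether a stroke occurred.
- **Prognostic model and risk assessment tool development.** The modelled outcome is "the 90 day occurrence of any stroke", which is binary. Predictors come from the initial specialist review. Internal validation is by bootstrap.
- **Sample size (Study A).** The inflation from 2574 to 2709 is explained as "Inflating for a 5% loss in case of routine data access difficulties" or an 'unclear' label on an outcome event.
- **Cohort description and stroke risk.** The two diagnosis groups are compared on documented hospital admission for stroke within 90 days. Adjudication status is not mentioned.

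**The concern.** A prediction model should be developed on everyone who meets the entry criteria. Here, membership of the development set depends partly on what happened after entry. A participant with no recorded event can never be 'unclear'; a participant with a recorded stroke, TIA or migraine can be. That is selection on outcome-related information.

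Two kinds of dispute fall under the rule. In a stroke-versus-non-stroke dispute the outcome really is uncertain, and exclusion may remove true strokes from a model that could have very few. In a TIA-versus-migraine dispute both parties agree that there was no stroke, so the modelled outcome is known and there is no reason to lose the participant.

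The bootstrap resamples the filtered data, so it can correct for overfitting but cannot detect who was filtered out. External validation is not planned (Strengths and limitations; Discussion), so nothing later in the project would expose the effect either.

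**Working it through.** **1. Reproduce the plan's figures.** Inputs from Sample size: 1% and 0.015%, two-sided 5%, 90% power. The two-proportion formula gives 1092 per group without continuity correction. With it, n' = (n/4)·[1 + √(1 + 4/(nΔ))]², where Δ = 0.01 − 0.00015 = 0.00985. The result is 1287 per group, 2574 in total, as stated. Inflation: 2574/0.95 = 2709.5, against 2709 stated. The allowance is 2709 − 2574 = 135 participants. The arithmetic is sound.

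**2. Expected strokes in 2574.**
- Planning rates: 1287 × 0.01 + 1287 × 0.00015 = 12.87 + 0.19 ≈ 13.1, an overall risk of about 0.51%.
- 10% scenario: 1287 × 0.10 + 1287 × 0.00015 = 128.7 + 0.19 ≈ 128.9, about 5.0%. This agrees with the stated minimum of 128.

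**3. Weight of each dropped true stroke.**

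| True strokes dropped | Share of 13.1 | Share of 128.9 |
|---|---|---|
| 1 | 7.7% | 0.8% |
| 3 | 23% | 2.3% |
| 5 | 38% | 3.9% |

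**4. Direction of the effect.** Let N be participants, T true strokes, U excluded cases and f the fraction of those that are true strokes. Risk in the retained set is (T − fU)/(N − U). This is below T/N exactly when f > T/N. Predicted risk is therefore too low if the excluded cases hold strokes at more than the cohort rate (0.51% or 5.0%), and slightly too high otherwise. That f is larger is plausible for stroke-versus-non-stroke disputes, but the documents give neither U nor f.

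**5. Illustration, assuming U = 10 (T rounded to 13 and 129).**

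| Fraction truly stroke | T = 13 (true 0.505%) | T = 129 (true 5.01%) |
|---|---|---|
| 0 | 13/2564 = 0.507% | 129/2564 = 5.03% |
| 0.5 | 8/2564 = 0.312% | 124/2564 = 4.84% |
| 1 | 3/2564 = 0.117% | 119/2564 = 4.64% |

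The first row is the case of pure TIA-versus-migraine disputes: overall risk hardly moves.

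**6. What bounding would show in the middle row.** Counting all ten as non-stroke gives 8/2574 = 0.311%, and all as stroke gives 18/2574 = 0.699%. The corresponding figures for T = 129 are 124/2574 = 4.82% and 134/2574 = 5.21%. The true values lie between the bounds. Exclusion (0.312%; 4.84%) gives almost the same answer as calling every disputed case a non-stroke, without saying so.

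**7. Which analyses are affected.** The adjudication section removes 'unclear' cases from model development only. Sample size counts them as loss against a calculation made for the group comparison. The section defining that comparison sets no adjudication condition. The three places do not settle whether these cases leave the comparison. 'Case' could also mean an event or a participant; the loss allowance points to participants.

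**The case against.** The best defence is that the rule is narrower and its harm smaller than it looks. The section heading refers to stroke diagnosis, and Sample size ties the label to outcome events, so the authors may have meant disputed strokes only. That is a fair guess at intent, but the operative sentence is triggered by any disagreement across three labels, so it needs rewording. The full statistical analysis plan may add sensitivity analyses. Even so, the primary exclusion is fixed here.

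The defence is right against several stronger readings that a reader might infer:

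- *The model is built on clear-cut presentations.* No. The label attaches to a later event. An ambiguous entry presentation stays in unless a subsequent event is disputed.
- *Discrimination is flattered.* Nothing in the documents allows this to be calculated.
- *The masking is undone.* A returned case suggests that the site differs, but with three labels it does not state the site's diagnosis, and it does not reveal the entry diagnosis. That the hospital knows the entry diagnosis is itself an inference.
- *The loss may exceed the 5% allowance.* To pass 135 participants one must combine the top ends of two assumed ranges: 20% with a recurrent episode and 30% of those disputed gives 2574 × 0.20 × 0.30 = 154. Choosing 10% and 20% gives 51. Neither range has a source in the documents. Even dropping 154 non-strokes moves risk only to 13/2420 = 0.537% or 129/2420 = 5.33%.
- *The group comparison loses power.* By the plan's own formula, power falls from 90% to about 80% or 73% if 20% or 30% of strokes are lost. Those losses are unsourced and matter only if 'unclear' cases leave that comparison.

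**Conclusion.** The concern holds in a limited form. The rule excludes participants on a label that only those with a recorded follow-up event can receive, and the planned internal validation cannot reveal the consequence. As worded it also discards TIA-versus-migraine disputes whose modelled outcome is known; this is needless loss with little effect on overall risk.

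The size and direction of any bias are not established. Predicted risk would be too low if disputed cases contain true strokes at more than the cohort rate. How much this matters depends on the event count: about 7.7% of events per dropped stroke at the planning rates, and about 0.8% at the 10% rate. The plan cannot rely in advance on the more favourable count. The 5% allowance restores numbers but does not correct a selective loss, and the handling of 'unclear' cases in the group comparison is unsettled.

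**What to change.** 1. Define 'unclear' on the stroke versus non-stroke axis only, and count TIA-versus-migraine disputes as non-stroke.
2. Keep every participant in model development, using the masked panel's majority classification of stroke or non-stroke. Five members give a majority on a binary question when all vote.
3. Refit the model twice as sensitivity analyses, with all 'unclear' cases counted as stroke and then all as non-stroke. Report the number of such cases by diagnosis group.
4. State the same handling for the comparison between diagnosis groups, and align the adjudication, sample size and cohort analysis sections.

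The cost is a change to the adjudication rule and two extra model runs, with no new data or staff. The downside is that a few outcomes will rest on a panel majority and not on agreement between panel and site. There is time: the Discussion reports 586 participants enrolled in November 2025, and follow-up completes in February 2027 (Project timeline).

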### Safety evaluation

As this observational study involves only verbal discussion and collection of routinely available data, a safety evaluation is not being conducted.

### Study withdrawal

No specific withdrawal criteria have been pre-set. Participants may withdraw from the study at any time for any reason. Data collected prior to withdrawal will be used in the study analysis.

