#### Population

Inclusion criteria:

Adults with migrainous symptoms reviewed as suspected TIA by a TIA/stroke service.Initial review conducted within 1 week of last symptoms.Following initial review, a specialist clinician symptom-based diagnosis is either possible migraine or possible TIA with migrainous symptoms.At least 40 years old.Able to provide informed research consent.

Exclusion criteria:

Suspected/confirmed TIA without any migrainous features.Clear alternative diagnoses after initial review e.g. seizures.Previous stroke.Referral already made or planned for surgical intervention to prevent stroke e.g. carotid endarterectomy or atrial septal defect closure.Currently under secondary care review for the same neurological symptoms.Cognitive difficulties preventing consent and/or description of subjective symptoms.Life expectancy <90 days.Day 90 follow-up is not possible e.g. resident outside of the service boundary.

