### Statistical analysis

#### Cohort description and stroke risk

Data will be presented for the total cohort, specialist clinician more likely diagnosis of migraine group and specialist clinician more likely diagnosis of TIA with migrainous symptoms group. This will include:

Summary descriptive statistics for baseline characteristics, investigations and treatments.Proportions suffering first hospitalisation for stroke by 90 days.Number and timing of stroke events by 90 days (in case of multiple events).Clinical characteristics of stroke events (including clinical and radiological subtype; symptom severity; emergency treatments received).

The proportion of patients experiencing any stroke, defined as at least one clinically documented stroke hospital admission during the next 90 days, will be compared between the specialist clinician more likely diagnosis of migraine group versus the TIA with migrainous symptoms group.

Specialist diagnosis, treatments and 90 day stroke rate across all study patients will also be reported according to:

The professional background of the clinician performing the assessment.The mode of assessment (in person vs remote).Other important service characteristics (eg, referral volume).

Exploratory analyses may also consider:

The clinician confidence rating for their diagnosis (very high/high/uncertain) for migraine or TIA with migrainous symptoms.Patients with single versus multiple stroke events.

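### The 90-day endpoint counts only admitted strokes, so a fatal stroke without admission is a non-event by definition and may never be identified

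*Protocol article*

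**What the plan says.** **Endpoint.** Under Cohort description and stroke risk, any stroke is "defined as at least one clinically documented stroke hospital admission during the next 90 days". The second study objective uses the same admission wording. The section on prognostic model development then takes the 90-day occurrence of any stroke as the model outcome.

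**Data.** "The day 90 data are collected from routine medical records". Table 2 has a stroke block that opens "If a stroke(s) has occurred, the following are obtained: Date/time of stroke", followed by severity, location, type, investigations and treatments. That block does not mention admission. Death appears separately, as "Vital status at day 90 (alive/deceased"; the table lists no date or cause of death.

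**Adjudication.** The panel reviews "all episodes of stroke, TIA or migraine recorded by participating hospital sites between study entry and day 90". Deaths are not mentioned as a reason for review.

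**Withdrawal.** "Data collected prior to withdrawal will be used in the study analysis". The section does not say whether the day-90 record check still takes place after withdrawal, or how a participant without it is handled.

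**The concern.** The project aims to define 90-day stroke risk and to build a tool that predicts it. A stroke that kills before admission is among the most severe outcomes such a tool should anticipate, yet the stated definition leaves it out. The data items and the panel's remit, as described, would not reliably bring it to light either.

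If such strokes occur, the reported 90-day risk is too low, and the model treats as stroke-free some participants who had the outcome. Here the misclassification is caused by the outcome itself, so it cannot be assumed to fall at random. Few events are expected at the planned rates, so each one matters.

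This is a matter of endpoint and data collection, not only of analysis. An analysis plan cannot classify a death whose date and cause were never recorded.

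**Working it through.** **1. The plan's own figures.** Inputs from the Sample size section: p1 = 1% (TIA with migrainous symptoms), p2 = 0.015% (migraine), 90% power, two-sided 5%, equal groups.

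- Difference d = 0.01 − 0.00015 = 0.00985; mean p = 0.005075.
- Pooled-variance formula: n = [1.96·√(2·0.005075·0.994925) + 1.2816·√(0.01·0.99 + 0.00015·0.99985)]² / 0.00985², about 1092 per group.
- Continuity correction: n/4 · [1 + √(1 + 4/(n·d))]² = 1287 per group, or 2574 in total. This matches the article.
- Inflation: 2574/0.95 = 2709.5, stated as 2709.

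The sample size is not in dispute. It is reproduced because the event count below rests on the same rates.

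**2. Expected events.** 1287 × 0.01 + 1287 × 0.00015 = 12.87 + 0.19 = 13.06, about 13 strokes. In the article's other scenario (10% in the TIA group), at least 128 events are expected.

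**3. Each kind of participant under the stated rules.**

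| Course within 90 days | Table 2 as summarised | Panel | Endpoint |
|---|---|---|---|
| Stroke, admitted, then dies | Stroke block completed with date | Yes | Event (correct) |
| Fatal stroke, not admitted, stroke noted in the record | Stroke block can be completed | Can be reviewed as a site-recorded episode | Non-event, because no admission |
| Fatal stroke, not admitted, hospital record shows only the death | Deceased only | No route | Non-event, and not identified |
| Death from another cause | Deceased | Not needed | Non-event (correct) |
| Withdrawal before day 90 | Not stated | Not stated | Not stated |

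The second and third rows are the defect. In the second, the table captures a stroke that the definition then discards. In the third, the stroke is not seen at all.

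The model section does not settle the matter. If any stroke carries its defined meaning there, the model inherits the admission restriction. If it carries its ordinary meaning, the model and the group comparison have different outcomes.

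**4. Size per missed stroke.** With m missed strokes in addition to those counted, the share of true events missed is m/(counted + m).

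- Planned rates, m = 1: 1/(13.06 + 1) = 7.1%.
- 128-event scenario, m = 1: 1/(128 + 1) = 0.8%.

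The documents give neither a 90-day death rate nor the share of deaths due to unadmitted stroke, so m itself cannot be derived from them.

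**The case against.** The strongest reply is that this is a condensed article. Table 2 is introduced as a summary, so the full case report form may hold a date or cause of death, and missing outcomes normally belong in the analysis plan. Strokes are recorded separately from vital status, so a stroke admission before death is captured. The exclusion "Life expectancy <90 days" removes participants expected to die. Because the trigger in Table 2 is a stroke and not an admission, an unadmitted fatal stroke noted in the record could still reach the panel.

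Much of this stands. It limits the claim about identification to what may happen. It does not touch the definition, which is stated twice and requires an admission whatever the form collects. The life-expectancy exclusion does not remove unexpected stroke deaths.

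A reader might also infer more than the text supports:

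- *Withdrawn participants are counted as stroke-free.* The article does not say so, nor that record review stops at withdrawal. Data kept from before withdrawal can serve the baseline descriptions alone. The sentence beginning "Inflating for a 5% loss in case of routine data access difficulties" treats unobtainable outcomes as losses. It does not name withdrawal, but it points towards exclusion and not towards coding as non-events.
- *Deaths in general lack a usable stroke outcome.* Table 2 records strokes independently of vital status, so this is not so.
- *Deaths from other causes require a competing-risk analysis.* When everyone is followed to day 90 or death, the cumulative incidence of stroke at day 90 equals the raw proportion with a stroke. A death from another cause is correctly a non-event.

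**Conclusion.** The point holds for fatal stroke without admission. The stated endpoint excludes it, and neither the death item in Table 2 nor the panel's remit, as described, ensures that it would be found. The result can only be an understated stroke risk and some outcomes wrongly labelled for the model.

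One such stroke would be about 7% of true events at the planned rates, and under 1% in the 128-event scenario. No estimate of the number is possible from the documents. The first figure assumes equal groups of 1287 and the stated rates of 1% and 0.015%. The part about identification also assumes that Table 2 reflects the full data collection.

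On withdrawal, the text is merely silent. Clarifying it is a worthwhile small improvement, not the correction of an error.

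**What to change.** 1. Define the endpoint, in the objectives and in the analysis section, as an adjudicated stroke within 90 days: either a documented stroke admission or a fatal stroke, whether or not admitted. State that the prediction model uses the same outcome.
2. Add date of death and recorded cause of death to the day-90 data, if the full form does not already hold them.
3. Send every death with stroke as a possible cause to the existing panel, blinded as already planned to the site diagnosis and to the entry diagnosis.
4. Secondary: amend the withdrawal section so that a participant who withdraws is asked whether the single day-90 record check may still be done.

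**Cost.** Two data fields, a minor amendment (including the withdrawal wording) and a few more panel cases. Some deaths with little clinical information may be labelled unclear; the 5% allowance already covers that label. No extra patient contact is needed for the death items. At submission in November 2025, 586 of 2709 participants were enrolled and recruitment was projected to run to November 2026. The change can therefore apply to most of the cohort, and because follow-up uses routine records, earlier deaths can probably be back-filled.
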